## Abstract

**Background:**

The impact of adverse childhood experiences (ACEs) has been the focus of most studies for the past decade. There is an indication that developing resilience can help youth overcome these ACEs.

**Objective:**

This article presents a study protocol for a randomized controlled trial (RCT) to investigate the effects of a resilience-building intervention on psychological well-being, coping strategies, stress, quality of life, resilience, resource finding, and resilience among individuals affected with ACEs in Malaysia.

**Methods:**

The is a 2-armed, single-blind, RCT, whereby 50 participants (25 in each group) with ACEs will be randomly assigned to intervention and control groups. The former will be exposed to a resilience-building program (R2), which entails a multisystemic approach to resilience and recognizes the importance of rugged qualities and access to resources among individuals affected with ACEs. The intervention will be delivered via internet-based by a facilitator and broadly divided into 5 sessions, focusing on self-exploration and social support, coping techniques and coping skills, resource finding, spirituality, and resilience building. Meanwhile, the control group participants will not receive any form of intervention. Saliva samples will also be collected from both groups and assessed for salivary cortisol levels. Outcome measures will be assessed during baseline and postintervention using validated instruments. Another follow-up measurement will be conducted 4 weeks later.

**Results:**

The clinical trial has been registered with the Australia New Zealand Clinical Trials Registry. Ethical approval was obtained from the Research Ethics Board at the National University of Malaysia (UKM PPI/111/8/JEP-2021-894). A total of 28 participants have been recruited to the RCT Participant recruitment will be completed by January 2025. The final analysis will be conducted by March 2025.

**Conclusions:**

This is among the first studies to provide evidence in the context of RCTs for resilience-building intervention that combines self-report and physiological measures (ie, saliva and heart blood pressure) among individuals with ACEs. The findings will assist relevant authorities in the health and policy sectors to develop effective strategies for addressing the negative impacts of ACEs on the vulnerable population in Malaysia.

**Trial Registration:**

ACTRN12622000604707; https://www.anzctr.org.au/Trial/Result/DataSharingStatement.aspx?id=383614

**International Registered Report Identifier (IRRID):**

DERR1-10.2196/56826

## Introduction

### Background

Adverse childhood experiences (ACEs) are stressful or traumatic events faced by individuals that could have a pervasive impact throughout the developmental stages of their lives through psychological and physiological mechanisms, particularly when the consequences are neglected [1]. ACE can have profound effects on individuals of all ages [2,3]. These experiences may culminate in disrupted development of brain areas that are stress-sensitive [4,5], which are reflected in behavioral alterations.

For example, individuals with ACEs may face challenges with emotion regulation, thereby leading to diverse negative consequences such as difficulties with interpersonal relationships, alcohol, and smoking habits [6,7]. Overall, these events are associated with obesity, depression, suicide, anxiety, heart attack, chronic health problems, chronic obstructive pulmonary disease, asthma, stroke, cancer, and unemployment [8,9]. Apart from emotion regulation, ACE survivors’ experience deficits in several domains of executive functions [10], which impact their well-being and psychological health [11]. Evidence suggests that individuals with ACEs, particularly children and young adults, are disadvantaged in terms of coping with increased stress relative to their peers without such bad experiences [12]. Since young adults are still experiencing biological and psychosocial development, the consequential impacts of ACE can be profound during adolescence and young adulthood [12].

Mental health problems are common among children and adults, which are predominantly presented as depression or anxiety and are characterized by frequent comorbidities [13]. Studies have demonstrated that ACEs represent an important predictor of emotional problems [14]. Previous research has documented several underlying events for the association between emotional problems and early ACEs among young children and adults [13,14]. For instance, individuals with a history of early ACEs were more accurate in recognizing threatening stimuli [15], constituting an adaptive response in harmful conditions. Nevertheless, it can heighten the risk of mental health disorders over time [16]. While individuals with ACEs are more likely to adopt maladaptive emotional regulation skills such as disengagement, expressive suppression, and rumination, they are less likely to perform successful activities such as cognitive appraisal [15], thereby leading to early emotional anomalies [16].

Specifically, ACEs also constitute a significant barrier to an individual’s capacity for resilience. Resilience depicts the resources, capability, and processes available to a system or an individual to adapt successfully in the face of challenges or adversities [17-19]. Resilience encompasses the factors that facilitate positive adaptation and navigation toward resources to sustain well-being in the context of adversity [16]. Therefore, researchers have developed an interest in resilience intervention as a potential approach to addressing the negative impacts of ACEs [19]. For instance, cognitive behavioral therapy (CBT) has been used in resilience interventions in ameliorating health problems, particularly among adults with a history of ACEs [19-21]. Hence, building resilience in individuals with adversity in the context of psychological intervention offers a new approach to managing individuals with ACEs.

### Adverse Childhood Experiences and Negative Consequences Among Children and Adults in Malaysia

ACEs refer to neglect, abuse, and dysfunctional households that may be deleterious to a person’s health and well-being. Research conducted in Malaysia has depicted an increasing frequency of child abuse and neglect cases, which are typical examples of ACEs that may impact negatively on physical and mental health [22]. ACEs also contribute to the growing health care expenditure, as the health consequences of ACEs reportedly accounted for 2% of the gross domestic product [23].

Nevertheless, information on the prevalence and negative impacts of ACEs among children and adults in Asia, specifically Malaysia, is scarce due to limited research. A recent study revealed a high prevalence of various ACEs among university students in northeast Malaysia, with a report of emotional abuse, emotional neglect, physical abuse, and sexual abuse occurring in 30.2%, 29.2%, 28.7% and 9.1% of the studied population [22]. High-risk behaviors (HRBs), particularly physical inactivity and community violence were recorded among 39.3% and 54.5% of the students, respectively [22].

Apart from HRBs, depression has been identified as a consistent outcome of ACEs among young adults in Malaysia [24,25]. Young individuals from Shah Alam, Malaysia, exhibited a high level of depression and ostracism, which was associated with ACEs. Early psychological mistreatment such as parental neglect of a child’s needs can lead to poor mental well-being [25], externalizing and internalizing problems, as well as anxious and avoidant attachment styles, making it challenging for children to develop a sense of belonging and feeling ostracized [26,27]. Therefore, early life traumatic events and ignorance appear to have strong influences on psychological well-being among this vulnerable population.

Besides the younger population, older adults in Malaysia have also been shown to be affected by ACEs, which may ultimately transit into elder abuse [28]. Furthermore, the risk of elder abuse increased with the cumulative number of ACEs. The results depict how early life adversities play an important role in older adults’ victimization. Recognizing the possibility that vulnerability to maltreatment can persist throughout the life course of elderly individuals is critical when attempting to address the problem through emotional and social support.

### Resilience-Building Interventions for Individuals With Adverse Childhood Experiences

Resilience is considered to be pertinent in the association between emotional problems and ACEs. Studies have depicted that resilience is a protective factor that can propel an individual to successfully address adverse experiences [29]. Thus, resilience is regarded as playing a protective role in the relationship between emotional disorders and ACE [29-31].

ACEs constitute a public health crisis that requires a wide range of interventions due to their high prevalence and impact on health disparities [31,32]. Resilience interventions are typical examples of CBT that are effective in ameliorating mental health disorders faced by individuals with ACEs [15]. According to Iniguez and Stankowski [33], ACE research has yielded strong evidence to support claims that “resilience resources and well-timed interventions to promote resilience can ameliorate the negative effects of ACEs” [33].

Chandler et al [21] demonstrated the feasibility and efficacy of an empower resilience intervention to enhance resilience and health behaviors among young adults with a history of ACEs. By using a 2-arm pre-post repeated measures design, young adults in the intervention group recorded significantly higher scores for building strengths, creating support connections, and reframing resilience. Meanwhile, a face self-help app designed by Brodbeck et al [34] and based on cognitive-behavioral principles, is currently being tested for its efficacy in promoting resilience and well-being in emerging adults with a history of ACE. MacIsaac et al [35] also evaluated the effects of an innovative, smartphone app-based resilience intervention on first-year university students’ self-regulatory skills (ie, emotion regulation and executive functioning), and the mediating role of emotion regulation. After 4 weeks of using the app, students’ emotion regulation and depressive symptoms improved significantly, with a faster rate of change in emotion regulation among those with more ACEs. Thus, evidence suggests that app-based resilience intervention can assist young adults with ACE by improving their emotion regulation skills and mitigating depression.

Systematic review findings depict that most interventions for addressing ACEs focused on psychological interventions and mental health outcomes, and cognitive-behavioral therapy has been consistently found to be effective in mitigating the negative impacts of abuse [36]. On the other hand, findings from interventions involving psychological therapies, specific support such as parent training, and broad support interventions are generally inconclusive despite some promising results [36]. In summary, significant gaps exist in the available evidence on interventions for ACEs, with most research focusing on individual psychological effects while neglecting the social pathways which may indirectly influence the negative impacts of ACEs. Several areas such as social relationships, life circumstances and health behaviors are examples of several negative impacts of ACEs that are still under investigation in most intervention research [34-36].

Building upon the global view on ACE research and resilience-building interventions, the Malaysian context must be taken into account in order to develop an effective intervention to address the problem of ACEs among children and young adults. Literature findings from the studies conducted in Malaysia have shown that ACE is a multifactorial problem that requires a multidimensional approach, rather than focusing on one individual aspect [22,23]. Such an approach is well-described in the multisystemic model of resilience developed by Ungar [8], highlighting the capacity of biopsychosocial and social-ecological systems to support external and internal conditions for well-being, as well as improving diverse populations’ quality of life. Thus, resilience encompasses the process whereby individuals harness the resources that are necessary for them to function optimally and seek resources to be provided using meaningful approaches, either contextually or culturally [8].

Interventions that emphasize individual change without considering the environmental domain may yield short-term benefits [37]. Hence, intervention should have a dual focus, encompassing personal and environmental change. For instance, a child’s resilience is a product of both their capacity to cope effectively under stress and the capacity of their physical and social environments to facilitate positive development. Under conditions of normal stress, individual ruggedness may be sufficient to support well-being; nevertheless, resources become more important and required as the individual experiences greater barriers to functioning. These 2 broad aspects form the foundation of the multisystemic perspective of resilience “R2,” which was coined to affirm the need to mitigate both the rugged qualities of individuals and their access to resources) [38].

Research has shown that individuals with more internal capacities such as problem-solving, self-regulation, and positive future orientation are more likely to harness opportunities for relationships and exploit such opportunities for academic or financial success [39,40]. Likewise, higher levels of motivation to execute life tasks and being more optimistic were observed among individuals with better access to external resources [41,42]. These findings reflect the dynamicity of resilience, whereby individuals interact with the world around them to make the best use of available resources despite exposure to adversity or atypical stress.

As highlighted in the reviewed resilience-building interventions for ACEs, while some target the public and common adversities like job burnout [43] and stress [44], others are aimed at specific groups, such as chronically diseased individuals [45], employees returning to work [46], and health care workers [47]. These interventions are delivered using diverse methods, ranging from phone apps to web-based tools or printed manuals, and duration may be as short as single-day workshops to weekly or monthly sessions. However, a recent meta-analysis revealed that such interventions have a small to moderate effect on improving resilience [44,47]. Existing resilience interventions also differ in terms of the targeted protective factors, such as self-efficacy, problem-solving skills, and cognitive flexibility, with most focusing on rugged factors. Only a few interventions consider resources that are external to individuals with ACEs [48]. Accumulated evidence suggests little to no data on interventions that explicitly target both coping strategies and ways of creating better-resourced environments around individuals with ACEs.

Hence, this study will modify and implement an R2 resilience program based on a resilience-building intervention designed with the principles of implementation science [38]. The multisystem aspect of the intervention allows it to focus on multiple systems for the individual’s change process and adaptation process around life circumstances. It is a curriculum-based approach that integrates all the well-researched factors and presents equal emphasis on the surrounding environments to the individual [8,38]. Thereafter, the factors and aspects can be modified and implemented into the resilience-building intervention accordingly. This study aims to explore the effects of the resilience-building intervention on mental health, stress, resilience, and resource finding among individuals affected with ACEs in Malaysia.

## Methods

### Study Design and Setting

This is a 2-armed, single-blinded, randomized controlled trial (RCT) that will be conducted among Malaysian youths with ACEs at the Department of Clinical and Health Psychology, National University of Malaysia. Briefly, the intervention group includes an evidence-based curriculum and components such as emotion regulation, active coping and goal setting, cognitive flexibility, mindfulness-based stress reduction, social support, self-exploration, resources and navigation, and finally, spirituality and religion. Participants in the control group will not receive any form of intervention. The main outcome of this study is resilience among youths with ACE while the secondary outcomes include coping, psychological well-being, quality of life, subjective stress, perceived stress, personal resources, and adult resilience. These variables will be evaluated at baseline and postintervention. Intention-to-treat analysis will also be performed. This clinical trial has been registered with the Australia New Zealand Clinical Trials Registry (trial Id: ACTRN12622000604707).

#### Sample Size

Sample size calculation was performed using G*power 3.1 software (Heinrich-Heine-Universität Düsseldorf). By assuming a study power of 0.8, 95% CI (α=0.05), and a moderate effect size of 0.25 as recommended by Ferguson (2009), the *F*-test was selected alongside repeated measures ANOVA with in-between interaction, with 2 groups and the number of measurements. Thus, a total sample size of 36 was obtained, reflecting 18 participants per group. We considered a high drop-out rate of 50% as several individuals may be unwilling to participate given the adverse effects of ACEs and confidentiality in sharing experiences with the researchers. Therefore, the sample size was increased to 50, amounting to 25 participants per group.

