#### Time Points for the Primary Outcomes and Retention

Premeasurements will be conducted at baseline, whereas postmeasurements will be collected after the fifth session as shown in Figure 1. Participants will be given Ringgit Malaysia 50 after the third and fifth sessions of the intervention to ensure they do not drop out of the study. Another follow-up will be conducted 4 weeks after the Intervention.

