### Data Analysis

All data management and statistical analysis will be conducted using SPSS (version 26; IBM Corp). Data management will be performed by screening for missing data and checking for potential outliers. Descriptive statistics will be used to assess the data normality and to summarize the pre and postintervention scores for each group at different periods. Mean and SDs will be provided for normally distributed data, followed by mixed ANOVA with repeated measures to compare the pre and postintervention mean scores between and within the groups.

The assumptions of ANOVA include randomly collected and normally distributed data, sufficient sample size, homogeneity of variances, and absence of violation and outliers. Levene’s test will be applied to test the homogeneity of variance. Mixed ANOVA benefits RCT design as it allows testing for 2 groups across 2-time points. Mixed ANOVA analysis aims to handle response outcomes conducted on the same experimental unit at a different time or under different conditions [57]. The differential effects of the intervention components will be tested with interactions between the component and time. These analyses will model random slopes and intercepts for participants, explore the fixed effects of the condition, and test the repeated measures over time. This type of analysis is advantageous by accounting for missing values through the maximum likelihood estimation method [57]. Effect sizes will be computed based on Cohen *d*.

In addition, the intention-to-treat analysis will be applied to analyze the participants according to their assigned groups. This analysis includes all participants and ignores noncompliance, protocol deviation, and withdrawal. The intention-to-treat analysis is a complete trial strategy for the design, execution, and analysis of RCT, focusing on the consolidated standard of reporting trial guidelines. Thus, the number of participants in each assigned group will be analyzed by the intention-to-treat principle.

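### The effect size of 0.25 called moderate in the sample-size calculation is a between-arm difference in change of about 1.0 SD, so the stated 80% power applies to a large effect

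*Protocol article*

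**What the plan says.** Under Sample Size, the calculation was run in G*Power with power 0.8, alpha 0.05 and "a moderate effect size of 0.25". The procedure was the F-test for "repeated measures ANOVA with in-between interaction, with 2 groups and the number of measurements", and "a total sample size of 36 was obtained, reflecting 18 participants per group". The planned enrolment is 50, or 25 per arm. The section gives no correlation between repeated measurements, and does not say what difference in scores 0.25 stands for.

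Under Data Analysis, mixed ANOVA is chosen because "it allows testing for 2 groups across 2-time points". The same section adds "Effect sizes will be computed based on Cohen" *d*. The section on time points and retention adds a third occasion: "Another follow-up will be conducted 4 weeks after the Intervention".

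The protocol describes the likely effect in two ways. The Introduction says of earlier programmes that "such interventions have a small to moderate effect on improving resilience". The Discussion (Principal Findings) expects moderate to strong effects from this intervention.

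**The concern.** An f of 0.25 is the familiar medium value for a one-way comparison of group means, where for two groups it corresponds to d = 0.5. It does not carry that meaning into G*Power's default within-between interaction. There, f measures the spread of the interaction cell effects, and the same 0.25 implies a treatment difference twice as large on the d scale.

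The trial will report Cohen d, so readers will set the results against the stated 80% power for a moderate effect. If moderate is read as about half an SD, the design is much less sensitive than the section says.

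**Working it through.** **Inputs.** From Sample Size: power 0.80, alpha 0.05, effect size 0.25 (read as Cohen's f because it enters a G*Power F-test), 2 groups, total N = 36, enrolment 50. From Data Analysis: m = 2 measurements. Assumed: correlation ρ = 0.5, with 0.3 to 0.8 shown as a range. SD means the outcome SD at one time point, equal across arms and occasions.

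**Step 1: reproduce the stated N.** The noncentrality is λ = f²·N·m/(1−ρ), with m−1 and (N−2)(m−1) degrees of freedom.

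- N = 34: λ = 0.0625 × 34 × 2/0.5 = 8.5, power 0.807. This is the smallest balanced total that reaches 80%.
- N = 36: λ = 9.0, power 0.830.
- m = 3, ρ = 0.5: N = 28.
- Exactly 36 also arises with m = 2 and ρ about 0.46, or with m = 3 and ρ about 0.33 to 0.35.

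The stated 36 is reproduced to within two participants, but the inputs behind it cannot be identified uniquely.

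**Step 2: convert f to a difference in change.** In a 2×2 layout, a between-arm difference in change of δ gives each cell an interaction effect of ±δ/4. Hence f = δ/(4·SD), and δ = 4 × 0.25 = 1.0 SD. The correlation does not enter.

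Check: at ρ = 0.5 the SD of the change score is SD × √(2(1−0.5)) = SD. A two-sample t-test on change with 17 per arm and d = 1 has squared noncentrality 17/2 × 1² = 8.5 and power 0.807, as in Step 1.

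For m = 3 with an effect that appears after treatment and persists, the arm difference follows the pattern 0, δ, δ. The SD of the interaction effects is (δ/2)·√(2/9) = 0.2357·δ, so f = 0.25 means δ = 0.25/0.2357 = 1.06 SD.

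**Step 3: power for δ = 0.5 SD.** Now f = 0.5/4 = 0.125. With m = 2 and ρ = 0.5, λ = 0.015625 × 36 × 2/0.5 = 2.25 at N = 36 and 3.125 at N = 50.

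| Correlation | Power, N = 36 | Power, N = 50 |
|---|---|---|
| 0.3 | 23% | 31% |
| 0.5 | 31% | 41% |
| 0.7 | 47% | 61% |
| 0.8 | 64% | 78% |

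At ρ = 0.5, 80% power for 0.5 SD would need N = 128.

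**Step 4: a check that does not need ρ.** Suppose power is exactly 80% at N = 36 for f = 0.25, as stated. With m = 2 that requires λ = 8.32. Halving the effect quarters λ to 2.08, and power falls to 28.9%. With m = 3 the corresponding figure is 26.5%.

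**Step 5: a larger effect, and the detectable difference (m = 2, ρ = 0.5).** For δ = 0.8 SD, f = 0.2. Then λ = 0.04 × 36 × 2/0.5 = 5.76 at N = 36 (power about 65%) and 8.0 at N = 50 (about 79%). The difference detectable with 80% power is 0.96 SD at N = 36 and 0.81 SD at N = 50.

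**The case against.** The strongest reply is that true power depends on the correlation in the data, which the protocol does not give, and on what moderate means, which it does not define. This stands. A reader might infer that the trial's real power is 31%, but the documents do not support that as a fact. It is the value for d = 0.5, two measurements, ρ = 0.5 and 36 analysable participants. The only numeric retest figure for an outcome measure that could guide ρ is an intraclass correlation of 0.81 over 7 days for the PSS-10. That is a secondary measure, and its interval is far shorter than the five weekly sessions. Even at ρ = 0.8, however, power for 0.5 SD stays below 80% at both 36 and 50.

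A second reply is that the sum is not wrong. That also stands: f = 0.25 does give about 36. Nor must 36 have come from the software defaults, since other inputs reach it too. The error lies in the description of the input.

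Third, a reader might infer that the trial will most likely be non-significant. The protocol does not support this either. Its Discussion expects moderate to strong effects, and at 0.8 SD power is about 65% with 36 and 79% with 50. The shortfall concerns effects near half an SD, which lie within both ranges that the protocol names.

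Finally, the unspecified number of measurements is a minor gap in a condensed article, and Data Analysis names two time points. The point does not depend on it, because three measurements with a sustained effect give about 1.06 SD.

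**Conclusion.** The point holds as a mislabelled effect size. With the two time points named under Data Analysis, the stated 80% power belongs to a between-arm difference in change of about 1.0 SD, whatever the correlation. That is conventionally large.

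For a difference of 0.5 SD, power with two measurements is about 31% with 36 analysable participants (range 23% to 64%) and about 41% with all 50 (range 31% to 78%). These figures rest on three assumptions: moderate means d = 0.5, there are two measurements, and the correlation lies between 0.3 and 0.8 with 0.5 as the central value. The 1.0 SD conversion needs only the two-by-two layout and G*Power's default definition of f. That definition is itself inferred from the close match to 36: if 0.25 had been used without the repeated-measures factor (λ = f²·N), the result would have been 128.

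**What to change.** Replace the effect-size statement in the Sample Size section with wording such as:

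*With 36 analysable participants, 2 measurements and an assumed correlation of 0.5, the trial has about 80% power for a between-arm difference in change of about 1.0 SD (about 0.8 SD if all 50 are analysable). Power for 0.5 SD is about 31% (23% to 64% for correlations 0.3 to 0.8) with 36 and about 41% (31% to 78%) with 50.*

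Drop the word moderate. If the team used another correlation or three measurements, it should state those and recompute the figures.

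The cost is a text change. Enrolment, randomisation, outcomes and analysis are unaffected. The downside is that the stated sensitivity becomes less favourable.

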As for missing data, drop-out in this study refers to participants who withdraw actively from the intervention post randomization. All cases of dropouts will be considered in the intent-to-treat samples since they have been randomized and included in the analysis. The extent and pattern of missing data will be assessed, and depending on the results, missing values will be replaced by using multiple imputations. The impact of the imputation of missing values will be further explored by conducting sensitivity analyses.

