## Results

This protocol, the informed consent and other relevant documents were reviewed and approved before the conduct of the research. Letters of extension and ethics approval were obtained from the Research Ethics Board at the National University of Malaysia. Amendments will be communicated to investigators, ethics review boards and publishing journals.

By January 2025, a total of 28 participants have been recruited into the study, comprising 14 in the intervention and 14 in the control group. Only 2 participants withdrew from the intervention group mainly due to a change in location and issues relating to data privacy and security. It is expected that participant recruitment will be completed by 30 January 2025. Preliminary analysis is ongoing, and the results suggest improvement in the investigated outcomes among participants in the intervention group across time. Final analysis will be conducted by March 2025, upon completing the data collection.

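### Randomising 50 does not cover the assumed 50% drop-out: keeping the required 36 would take 72, and 50 covers at most 28% loss of outcome data

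*Protocol article*

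**What the plan says.** Under Sample Size, the protocol article sets out the calculation: "By assuming a study power of 0.8, 95% CI (α=0.05), and a moderate effect size of 0.25", for a "repeated measures ANOVA with in-between interaction, with 2 groups and the number of measurements". It obtains 36 in total, 18 per group. It then adds an allowance: "We considered a high drop-out rate of 50% as several individuals may be unwilling to participate". The conclusion follows directly: "Therefore, the sample size was increased to 50, amounting to 25 participants per group".

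Three other places fix what these numbers mean.

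- The Abstract (Methods) says that the 50 are the participants to be randomly assigned, 25 to each group.
- Participant Recruitment and Randomization places consent and ACE screening before random assignment.
- The missing-data paragraph under Data Analysis defines the term: "drop-out in this study refers to participants who withdraw actively from the intervention post randomization".

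On experience so far, Results reports 28 recruited, 14 per group, and "Only 2 participants withdrew from the intervention group".

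**The concern.** A drop-out allowance should ensure that the required number still has usable outcome data after the assumed loss. Half of 50 is 25, which is 11 short of 36, so the step from 36 to 50 does not do this at the article's own rate.

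The reason given for the 50% does not fit either. People unwilling to take part refuse before randomisation, so they raise the number to be approached and not the number to be randomised. The article's own definition of drop-out is a post-randomisation one.

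Readers use this paragraph to judge whether a null result is informative. As it stands, they may believe that the trial can lose half its participants and still have its planned power.

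**Working it through.** **Inputs stated in the article.** Power 0.80, alpha 0.05, effect size 0.25 (read as Cohen's f), 2 groups, within-between interaction, 36 required, 50% drop-out, 50 randomised.

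**Inputs not stated.** The number of measurements m, the correlation rho between repeated measures, and the sphericity correction. Data Analysis speaks of 2 time points, while the schedule adds a 4-week follow-up, which makes 3 for the questionnaires. I take m = 2, rho = 0.5 (the software default) and no sphericity correction as the base case, and vary m and rho.

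**Step 1: reproduce 36.** The noncentral F calculation for the interaction with 2 groups uses

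- lambda = f² x N x m / (1 - rho)
- df1 = m - 1
- df2 = (N - 2)(m - 1)

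With m = 2 and rho = 0.5:

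- N = 34: lambda = 0.0625 x 34 x 2 / 0.5 = 8.5, power 80.7%
- N = 36: lambda = 9.0, power 83.0%

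The smallest even N is 34, within 2 of the stated 36, so I treat 36 as reproduced. With m = 3 and rho = 0.5 the answer is 28, which does not match.

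**Step 2: the drop-out allowance.** This step needs no assumption about m or rho.

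- Correct inflation: 36 / (1 - 0.5) = 72
- Common shortcut: 36 x 1.5 = 54
- Left after 50% loss from 50: 50 x 0.5 = 25
- Largest loss that leaves 36 of 50: 1 - 36/50 = 28%

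Neither formula leads from 36 to 50. The shortcut applied to 34 gives 51, but 34 is not the article's base figure.

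**Step 3: power if only 25 have outcome data.**

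| Setting | Power at 36 | Power at 25 |
|---|---|---|
| m = 2, rho = 0.5 | 83.0% | 66.8% (lambda = 6.25) |
| m = 2, rho = 0.459, set so that 36 gives 80% | 80% | 63.4% |
| m = 3, rho = 0.330, set so that 36 gives 80% | 80% | 62.5% |
| m = 3, rho = 0.5 | 90.6% | 76.0% |

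The range at 25 is therefore about 62% to 76%. A higher correlation would raise it (m = 2, rho = 0.7 gives 87.1% at 25), but 22 would then suffice and 36 would not be the requirement. Under any setting for which 36 is the smallest adequate number, 25 falls below 80%.

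**Step 4: experience so far.** Withdrawals are 2/28 = 7%. At that rate, 50 randomised leaves 50 x 26/28, about 46, and the base-case power is about 91%. With no loss, 50 gives 93.4%.

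**The case against.** **The 50% may mean refusal.** The reason given is unwillingness to take part. On that reading no randomised participant is lost, and 50 gives about 93% power in the base case. This does not rescue the paragraph. Refusers never enter the 50, so refusal is no reason to go from 36 to 50, and the article's definition of drop-out is post-randomisation. It does show that the loss of power follows from one reading of the rate.

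**Withdrawing from the intervention is not the same as missing outcome data.** This stands. The definition concerns withdrawal from the intervention, all randomised participants stay in the intention-to-treat sample, and maximum likelihood and multiple imputation are planned. Those methods do not restore unobserved post-intervention outcomes, but participants who stop sessions may still be assessed. Twenty-five with outcome data is therefore the worst case at a 50% drop-out rate.

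**Stronger readings that the article does not support.**

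- A reader might infer that power falls from 80% to 67%. That pairs the stated target with a modelled value. Like for like, the fall is 83% to 67%, or 80% to about 63%.
- A reader might infer that the trial will keep only 25. Reported withdrawals are 2 of 28, well within the 28% that 50 covers.
- A reader might infer that the article claims 80% power after 50% attrition. It states no power after attrition. The claim is only implied by the way 50 is derived from the 50% rate.

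**Conclusion.** The point holds as an inconsistency in the stated sample-size figures. A requirement of 36 with 50% drop-out leads to 72 randomised, not 50, and 50 covers at most 28% loss of outcome data. This part rests only on the article's own numbers and on reading drop-out as the loss that the increase was meant to offset.

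The effect on power is conditional. If half of the 50 had no outcome data, power at f = 0.25 would be about 67% with m = 2 and rho = 0.5, and about 62% to 76% across the settings examined. All of these are below the 80% target. The article gives no sign that losses are approaching that level, so this is a wrong statement of robustness and not evidence that the trial will be underpowered through drop-out.

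**What to change.** Keep the target of 50 and replace the drop-out sentences with text such as:

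> Randomising 50 leaves the required 36 analysable participants if post-randomisation loss of outcome data is at most 28% (a figure derived from the target of 50). It does not cover 50% loss, at which 25 would be analysable and power would be about 67% with 2 measurements and a correlation of 0.5 (range about 62% to 76%, depending on the number of measurements and the assumed correlation).

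Alongside this:

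- State the number of measurements and the correlation used to obtain 36, so that the range can be replaced by one figure.
- Remove unwillingness to participate as a reason for enlarging the randomised number, or move it to the number to be approached and screened.
- Note that withdrawals reported so far are 2 of 28 (7%), and keep the sentence conditional on 50 being reached, since 28 had been recruited at the time of the report.

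The cost is wording only, with no extra participants and no change to the analysis. The stated protection against drop-out becomes less favourable, but correct.
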